## **1. Lay Summary**

Major Depressive Disorder (MDD) is one of the largest health problems worldwide. Psychological treatments show variable outcome rates with approximately 50% recovery in 'gold standard' cognitive behaviour therapies (CBT's). More effective treatments for depression are needed. Metacognitive therapy (MCT) is a newer treatment for MDD that has produced promising results in preliminary studies. Hagen et al (submitted) showed very large effect sizes in a randomised trial comparing wait-list with MCT. In their study 70-80% could be classified as recovered. The next step is to compare MCT with CBT in a definitive trial.

In this study a large parallel randomised single-blind trial will be conducted comparing metacognitive therapy (MCT) and Cognitive Behavioural Therapy (CBT). Adult patients diagnosed with major depressive disorder (MDD) will be assigned to treatment consisting of up to 24 sessions of either CBT or MCT and the treatment terminated when remission is reached defined as two consecutive scores of  $\leq 8$  on Beck's Depression Inventory II (BDI-II). Patients will be followed-up for 6 months post-treatment.

## **2. Background and Rationale**

Depression is considered one of the largest health problems around the world. Several different medical and psychological treatments have been developed to treat the condition with mixed effects. Therapies for depression involve interpersonal therapy (Cuijpers, Geraedts, et al., 2011), Brief psychodynamic therapy (Driessen et al., 2015) and mindfulness-based therapies (MBSR and MBCT, (Gotink et al., 2015).

The most widely tested psychological treatment for MDD is cognitive behaviour therapy (CBT). CBT was first introduced by [name] T Beck (A. T. Beck, Rush, A.J., Shaw, B. F., & Emery, G. , 1979 ) and involves cognitive and behavioural strategies including restructuring of negative and biased thoughts and beliefs that the individual holds about the self, others and the future. Furthermore, CBT for MDD involves increasing levels of mastery and pleasurable activities. In CBT theory depression is caused by activated negative schemas (beliefs) e.g. "I'm unlovable" which colour the interpretation of experience and result in low mood.

The effect of CBT on MDD has been studied across multiple randomised controlled trials (RCT's) with moderate effect sizes (Cristea et al., 2015). A recent meta-analysis, however, reported that the effects of CBT as an antidepressant treatment has declined over the years (Johnsen & Friberg, 2015) suggesting that better treatments for depression are needed in order to enhance treatment outcome for this population.

A review of the literature shows that the majority of randomised trials give recovery rates of approximately 50% in ITT analysis for different psychological treatments. These include CBT, interpersonal therapy, antidepressant medication and supportive therapy. However, there are a number of biases, which make comparisons and conclusions challenging. These include treatment integrity, treatment duration and the lack of a valid and objective definition of treatment outcome and clinically significant change. The present trial is designed to overcome these biases and test MCT versus CBT in a definitive trial.

Metacognitive therapy (MCT) is a more recent treatment for depression. MCT is based on the Self-Regulatory Executive Function model (S-REF model) developed by Wells & Mathews (1994; 1996). According to this model psychological disorders are not caused by negative schemas but instead result from a style of thinking called the Cognitive Attentional Syndrome (CAS). In depression the CAS consists of voluntary mental coping strategies dominated by rumination/worry, avoidance, and mood monitoring along with other strategies that backfire and result in depressive symptoms. The cognitive attentional syndrome is driven by metacognitive beliefs such as the belief that rumination is a useful means of finding an answer to depression and the belief that depressive thinking is uncontrollable.

To date metacognitive therapy (MCT) for depression has been tested in a limited number of studies that have shown MCT to be a promising intervention that may improve on recovery rates. For example, Dammen et al (2015) implemented a group MCT intervention on 11 depressed individuals and found that 91% of them were recovered at follow-up (Callesen, Jensen, & Wells, 2014; Dammen, Papageorgiou, & Wells, 2015; Wells et al., 2009).

Jordan et al. (2014) conducted a randomised trial in New Zealand in which 48 depressed patients were randomised to either CBT or MCT. Effect sizes were moderate-to-large for both treatments

with no significant differences on primary measures. The number of participants meeting response criteria for each condition was slightly better in MCT (52%) than CBT (44%). In addition, follow-up analysis revealed that MCT produced greater changes in measures of improved executive control and spatial working memory (Groves et al., 2015). Several limitations were found in this study. First of all, Training or supervision in MCT was limited and post-hoc analyses suggested that MCT might have been adversely affected by comorbidity as 48% were suffering from social anxiety in the MCT condition compared to 28% in the CBT condition.

Hagen et al (submitted) conducted a RCT comparing MCT to a wait-list condition. Results from this trial demonstrated very large effect sizes for MCT. In this trial thirty-nine patients were randomly assigned to immediate MCT (10 sessions) or to a 10-week wait list period (WL). The WL-group received 10 sessions of MCT after the waiting period. Participants receiving MCT improved significantly more than the WL group with very large controlled effect sizes for both depressive ( $d = 2.51$ ) and anxious symptoms ( $d = 1.92$ ). Approximately 70-80% could be classified as recovered on the BDI-II at post-treatment and 6 months follow-up following immediate MCT, whilst 5% of the WL patients recovered during the waiting period. These findings suggest that a non-hybrid, pure version of MCT may be particularly effective.

The current proposed trial is designed to test MCT for MDD by comparing it to a bona fide benchmark treatment; CBT. The trial utilises a strict methodology intended to reduce potential biases encountered in earlier studies. Patients are allocated to a total possible number of treatment sessions with pre-set criteria for potential early termination. They receive up to 24 sessions of therapy or until they reach a predetermined agreed recovered state. Strict session-by-session manuals for both treatments, expert supervision in both CBT and MCT and objective definitions of recovery and relapse will be adopted using a conservative and clinical change index as defined by Jacobson and Truax (1991).

### **3. Study Aims and Measures**

The aims of the present study are as follows:

1. To assess the relative efficacy of MCT versus CBT in the treatment of patients with major depressive disorder. Primary outcome variables are: Becks Depression Inventory –II (BDI-II) and Hamilton Depression Rating Scale (HDRS)
2. To assess the relative efficacy of MCT vs. CBT in the treatment of patients with major depressive disorder on secondary outcome variables: Becks Anxiety Inventory (BAI), process variables (Rumination time measured by MDD-S) and negative/positive metacognitive beliefs (NBRS/PBRS) as well as schema-related content variables (The Dysfunctional Attitude Scale – (DAS)) will be used.
3. To determine if treatment effects are maintained over a 6 months follow-up period.
4. To investigate recovery rates and clinical significant change levels in CBT and MCT
5. To assess dropout rates, treatment adherence, and the quality of the therapeutic alliance in both treatment arms in order to detect any potential differences in MCT and CBT.

#### **4. Research hypotheses**

The null hypothesis predicts that there will be no significant differences in primary and secondary outcome variables or recovery rates in MCT and CBT at post treatment and at follow-up.

#### **5. Methods**

##### **5.1. Participants and sampling procedures**

Patients referred from their general practitioner (GPs) with a diagnosis of depression to a large Danish outpatient facility called CEKTOS (Center for Kognitiv Terapi) will be assessed for eligibility. In Denmark the NHS is partly funded by the state and partly by the patients themselves. Therefore, a payment of 315.00 Danish kr. pr. session will be administered for all participants in the trial. The study flow chart is presented in appendix 1.

### **5.2. Inclusion criteria**

- Patients from 18-70 years of age with a main or primary diagnosis of major depressive disorder (MDD) according to the Structured Clinical Interview for DSM-IV-TR, Axis I Disorders (SCID-I)
- Patients who agree to attend therapy in the trial and have not received other psychological treatments for the current depressive episode.
- Patients in combined medical treatment as long as they are stable or willing to remain stable on medication
- Patients who are willing and able to sign the informed consent

### **5.3. Exclusion criteria**

- Patients suffering from psychosis, substance abuse or bipolar disorder as determined by SCID I
- Patients suffering from borderline personality disorder as screened by SCID II
- Patients with organic brain syndrome or learning difficulty
- Female patients who are pregnant and close to giving birth
- Patients who have not responded favourably to a previous trial of either CBT or MCT

## **6. Outcome measures**

A battery of assessments will be administered by an independent assessor blind to treatment allocation at pre-treatment, post-treatment and at 6- months follow-up. The primary outcome measures are Beck's Depression Inventory (BDI-II) and the Hamilton Depression Rating Scale (HDRS). We chose both a self-rating scale and an interview-based scale in order to account for effects in different ways. In addition, several secondary self-report measures will be administered at pre-treatment, post-treatment and follow-up. The schedule of measures is presented in appendix 2:

### **6.1. Primary outcome measures:**

**Depressive symptoms (Beck Depression Inventory – BDI-II)**

The BDI was developed by Beck and his colleges in 1961 and has become one of the most widely used instruments for assessing the intensity of depression. The inventory has been revised several times and the most recent version is Becks Depression Inventory-II (A. T. Beck, Steer, R.A., Ball, R., & Ranieri, W., 1996). The BDI-II is a widely used reliable instrument to assess the severity of depressive symptoms. In fact, the BDI-II shows much better internal reliability than the BDI-I (Dozois, Dobson, & Ahnberg, 1998). It is a self-report inventory consisting of 21 items, where symptoms such as sadness, loss of pleasure, changes in sleep pattern, and worthlessness are measured and rated on a four-point scale ranging from 0 (not present) to 3 (severe). All the scores are summated to form a total score, where the maximum score obtainable is 63. A score of 0-13 indicates minimal depression, 14-19 indicates mild depression, 20-28 indicates moderate depression and 29-63 indicates severe depression.

### **Depressive symptoms (Hamilton Depression Rating Scale)**

The HDRS is a well-established and widely used rater-administered scale to measure the severity of depressive symptoms (Andrews & Williams, 2014; Hamilton, 1960; Williams, 1988). The scale consists of 17 items, which are grouped into different categories, such as depressed mood, suicide, insomnia, and somatic symptoms. Eight items are scored on a 5-point scale increasing in severity, where nine items are scored on a 3-point scale. The maximum score obtainable is 53. Scores of 0-17 indicates no depression, 8-13 indicates mild depression, 14-18 indicates moderate depression, 19-22 indicates severe depression, and above 23 indicates very severe depression.

## **6.2. Secondary outcome measures:**

### **Beck Anxiety Inventory (BAI)**

The BAI (A. T. Beck, Epstein, N., Brown, G., & Steer, R. A., 1988) is an inventory that measures the severity of anxiety, and was developed specifically to distinguish anxiety from depression. The inventory contains 21 items, which assess symptoms such as nervousness and fear of dying, where the items are rated on a 4-point Likert scale, which ranges from 0 (not at all) to 3 (severely). The maximum score is 63, where the cut-off point of clinical anxiety is 16 (Aaron T Beck & Steer, 1990). Higher scores on the BAI suggest a greater intensity of symptoms of anxiety. The BAI is viewed as an accurate measure of anxiety with high reliability and validity in non-clinical and clinical settings (Fydrich, Dowdall, & Chambless, 1992).

*Meta-cognitive scales:*

### **Major Depressive Disorder Scale (MDD-S)**

MDD-S is a short self-report scale designed to measure depression levels, meta-cognitive beliefs and maladaptive coping-skills over the past week. The scale was developed as an assessment tool to evaluate baseline levels and progress in MCT treatment (Wells, 2009b).

### **Metacognitions Questionnaire (MCQ-30)**

The MCQ 30 (Wells & Cartwright-Hatton, 2004) is a 30-item measure consisting of 5 subscales of beliefs which are: positive beliefs about worry, negative beliefs about thoughts concerning uncontrollability and danger, cognitive confidence, negative beliefs about the need to control thoughts, and cognitive self-consciousness (Wells & Cartwright-Hatton, 2004). Responses are rated on a 4-point Likert scale, which ranges from 1 (do not agree) to 4 (agree very much).. The scale has been found to have good construct and predictive validity and is responsive to treatment.

### **Negative and beliefs about rumination scales (NBRS)**

The NBRS is a 13-item scale that measures negative beliefs about the uncontrollability and danger of ruminating (Papageorgiou & Wells, 2003). The scale consists of 13 statements, such as ‘I will lose control if I ruminate too much’ and ‘ruminating makes me physically ill’. These statements are rated on a 4-point Likert scale ranging from 1 (do not agree) to 4 (agree very much). The NBRS show good internal consistency, validity and fit to the MCT model (Roelofs, Huibers, Peeters, Arntz, & van Os, 2010).

### **Positive beliefs about rumination scales (PBRS)**

The PBRS was developed to measure positive beliefs about rumination (Papageorgiou & Wells, 2002). The self-report scale contains 9 items consisting of statements such as ‘I need to ruminate about my problems to find answers to my depression’. Each statement is rated on a 4-point Likert scale ranging from 1 (do not agree) to 4 (agree very much). In studies examining the psychometric properties of the PBRS good internal consistency and validity have been demonstrated (Huibers et al., 2014; Roelofs et al., 2010)

### **Rumination Response Scale (RRS)**

The RRS is a subscale of the Ruminative response questionnaire, RRQ (Nolen-Hoeksema & Morrow, 1991), and measures the response styles to depressed mood, which are focused on ‘the self, on symptoms, and on possible causes and consequences of the mood. The scale consists of 22 items and contains statements such as ‘think about how sad you feel’ and is rated on a scale from 1 (almost never) to 4 (almost always). (Thanoi & Klainin-Yobas, 2015) tested the psychometric properties of the RRS on 747 undergraduates and found satisfactory reliability.

*Cognitive scales:*

### **Dysfunctional Attitude Scale (DAS)**

The DAS is a scale that measures negative cognitions in depression, and examines the dysfunctional attitudes the individual has towards the self and the world (Weissman & Beck, 1978). The scale consists of 40 items, where each item is rated on a 7-point Likert scale ranging from 1 (fully disagree) to 7 (fully agree). The maximum score obtainable is 280, where higher scores indicate a higher intensity and presence of dysfunctional attitudes. Reliability and validity data for the DAS support its use as a measure of depressionogenic beliefs in an adult population (Oliver & Baumgart, 1985)

### **Young’s Schema Questionnaire (YSQ-SF) - short version**

The YSQ contains 16 subscales that measure early maladaptive schemas (Young & Brown, 1994), which contribute to perceptions of the self, the world and others (Rijkeboer, van den Bergh, & van den Bout, 2005). The short version consists of 75 items out of the 205 items from the long version, and measure schemas such as emotional deprivation, abandonment, and vulnerability to harm (Young & Brown, 1994). Each schema is rated on a 6-point scale ranging from 1 (completely untrue of me) to 6 (describes me perfectly).

*Other measures:*

### **Co-morbidity (SCID I)**

The SCID-I (Spitzer et al., 1992) is a semi-structured interview to be administered by a clinician, and was used to determine presence of Axis I diagnoses. The semi-structured interview consists of an introduction and nine modules.

### **Patient-therapist alliance (Working Alliance Inventory, WAI)**

The WAI is a self-report instrument used to assess the quality of alliance between the therapist and the patient and can be administered by the therapist and the patient (Adam O Horvath & Greenberg, 1989a). This 36-item inventory is based on Bordin's theory of therapeutic alliance (Bordin, 1979), which also constitutes the three subscales of the inventory, which are: goals; the agreement of goals between therapist and patient; tasks; the agreement of the tasks throughout therapy to reach these goals; and bond, the direct relationship between therapist and patient, which involve factors such as mutual trust (Tracey & Kokotovic, 1989). Each item is rated on a 7-point Likert scale, where the options range from 1 (never) to 7 (always). The inventory has also demonstrated sufficient validity (Adam O. Horvath & Greenberg, 1989b).

### **Patients' expectancies about treatment outcome**

The Patient' expectancies about treatment outcome contains two questions, which ask about how logical the treatment seems to the patient during participation, and to what extent the patient feels the treatment will help them reduce their symptoms. Each question was rated on a 1-5 scale ranging from 'Not at all' to 'Very much'.

### **Objective measure (Concentration and attention subtests from the WAIS)**

Wechsler's Adult Intelligence Scale (WAIS) is one of the most widely used instruments to measure intelligence and cognitive functioning (Kaufman & Lichtenberger, 2005). The instrument contains a range of subtests that measure dimensions such as verbal comprehension, perceptual reasoning, working memory and processing speed (Wechsler, 2014)). This measure is included for analyses in a separate study and not for the main trial.

## **7. Ethical Considerations**

The present study uses the best-proven standards for CBT and MCT. All therapists are experienced clinical psychologists working under the Nordic Ethical Guidelines and according to good clinical

practice standards described at Dansk Psykolog Forening ([www.dp.dk](http://www.dp.dk)). The trial design and consent form was formally approved by the Danish ethics committee on the 13th of December 2010. All participants considered for the trial will be provided with written and oral information so that they can make an informed decision about participation. This trial will be conducted in compliance with the protocol approved by Manchester University and the Danish Ethics Committee ([www.cvk.im.dk/cvk/](http://www.cvk.im.dk/cvk/)).

## **8. Safety Reporting and Adverse events**

An adverse event can be defined as:

*Any unfavourable, unintended effect that occurs during a study (e.g. symptom, diagnosis, test finding), having been absent at baseline, or if present at baseline appears to worsen.*

Information related to an adverse event will be captured in the case file and will be regularly monitored by the research management group in line with Good Clinical Practice Guidelines. In the case of adverse events like suicide attempts or sudden accidents it was decided to take action and report and exclude patients from the trial in order to get them hospitalised. However, no adverse events were reported in this trial.

A serious adverse event (SAE), is any untoward medical occurrence that

- results in death
- is life threatening (including suicide attempts)
- requires hospitalisation
- results in persistent or significant disability/incapacity

SAE's will be reported to the ethical committee that gave a favourable opinion to the study where in the opinion of the chief investigators the event was related to the research procedures. The response to SAE's will be determined on a case by case basis and will be in line with local policies and procedures.

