## **9. Trial design and analysis**

The trial is a single blind randomised, parallel between-groups design with 6-months follow-up (See trial flow diagram and timeline [Trial Registration Number: ISRCTN82799488 - Meta-cognitive Therapy (MCT) versus Cognitive Behaviour Therapy (CBT) for Depression. An assessor will undertake HRSD ratings and will remain blind to treatment allocation. Randomisation lists will be drawn up independently and held outside of the study team.

Severity of depression and gender of participants will be used as stratification variables during randomization. Participants will be assigned to therapists within treatment modality based on therapist availability.

Patients will be allocated up to a maximum of 24 sessions of MCT or CBT and assessed at pre-treatment, mid-treatment, post-treatment and at 6-months follow-up.

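### Adverse events are defined over the whole study, but the only stated capture route is the case file, with no set question, time point or window, so the statement that none were reported cannot be read as absence of harm

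*Protocol*

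**What the plan says.** Section 8 of the protocol defines an adverse event as "Any unfavourable, unintended effect that occurs during a study (e.g. symptom, diagnosis, test finding), having been absent at baseline", and extends this to anything present at baseline that gets worse. On collection it says: "Information related to an adverse event will be captured in the case file and will be regularly monitored by the research management group". It names no question, no person who asks, no visit and no start or end of observation. A few lines later it gives a result: "However, no adverse events were reported in this trial".

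The study period is longer than therapy. The Lay Summary states: "Patients will be followed-up for 6 months post-treatment". Therapy itself has no fixed length. According to the Lay Summary, up to 24 sessions are offered, with "the treatment terminated when remission is reached defined as two consecutive scores of" 8 or less on the BDI-II. Section 2 says the same in other words: "They receive up to 24 sessions of therapy or until they reach a predetermined agreed recovered state".

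The Appendix 2 schedule has four columns (T1, sessional, T2, T3). It has no adverse event row and shows no contact between T2 and T3. Section 6 has an independent blinded assessor see both arms before treatment, after it and at 6 months.

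**The concern.** How events are elicited is a matter for the protocol, because an analysis plan cannot recover events that nobody asked about. Without a prompt, an event is recorded only if the patient volunteers it or someone happens to note it. The regular contact at which that is most likely is the therapy session, and the number of sessions depends on the score of a primary outcome scale.

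Two things are at stake. First, completeness: section 8 itself names suicide attempts and accidents as events of interest, and one that occurs during the 6 months after therapy has no prompted route into the record. Second, comparability: if one therapy reaches the stopping rule sooner, its patients have fewer contacts and a shorter total observation time, since follow-up is counted from the end of treatment. Raw counts by arm would then not be on the same footing. Both affect what the whole-trial statement of no adverse events can mean.

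**Working it through.** The protocol gives no figure for adverse event capture, so there is none to reproduce.

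**Step 1. Definition against collection.** The definition covers the whole study, while the stated route is a file with no window. No other section supplies a time point. The definition and the means of collection do not match in scope.

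**Step 2. How much study time has no prompt.** Assumptions: weekly sessions (the protocol gives no frequency) and 26 weeks of follow-up.
- A patient who stops after 8 sessions has a study time of 8 + 26 = 34 weeks, of which therapy is 8/34 = 24%.
- A patient who uses all 24 has 24 + 26 = 50 weeks, of which therapy is 24/50 = 48%.

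So about half to three quarters of a patient's study time lies after the last session.

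**Step 3. Are unequal treatment lengths foreseeable?** Inputs from section 9.1: post-treatment BDI-II means of 10 (MCT) and 14 (CBT), SD 7. The stopping threshold is 8. If scores are roughly normal (an assumption), the share at or below 8 is Φ((8 − mean)/SD):
- MCT: Φ((8 − 10)/7) = Φ(−0.29) = about 39%
- CBT: Φ((8 − 14)/7) = Φ(−0.86) = about 20%

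This is only a rough guide. The rule needs two consecutive scores, and the means come from separate earlier studies. It shows that if the planned effect exists, unequal contact is a likely consequence. It does not give treatment length by arm.

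**Step 4. Effect on raw counts.** With the same true weekly event rate in both arms, expected recorded events are proportional to weeks observed. The ratio, faster arm to slower arm, is f/s if capture ends with therapy and (f + 26)/(s + 26) if it continues to T3. All session averages below are assumed.

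| Weeks of therapy, faster v slower arm | Capture ends with therapy | Capture runs to T3 |
|---|---|---|
| 8 v 24 | 8/24 = 0.33 | 34/50 = 0.68 |
| 10 v 16 | 10/16 = 0.63 | 36/42 = 0.86 |
| 12 v 24 | 12/24 = 0.50 | 38/50 = 0.76 |
| 20 v 24 | 20/24 = 0.83 | 46/50 = 0.92 |
| Equal | 1.00 | 1.00 |

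Under a constant rate, dividing by the person-time actually observed returns every row to 1.00.

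**Step 5. What zero events would show.** With 64 patients per arm (section 9.1) and perfect capture, zero events leave a one-sided 95% upper limit of 1 − 0.05^(1/64) = 4.6% on the proportion of patients with an event. If only half of affected patients were recorded (an assumption), the limit on the true proportion would be 4.6%/0.5, about 9%.

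**The case against.** The strongest opposing case concerns what a reader might infer: that the arm which finishes sooner will look safer, by something like 37% (1 − 0.63). The document does not support that. It gives no treatment length by arm. It does not say that capture stops with therapy, and the case file is not described as a therapy file. The aims and hypotheses include no between-arm safety comparison. With zero events stated overall, no difference between arms can appear.

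A reader might also infer that any worsening after therapy goes unrecorded. That too is unsupported. The BDI-II, HDRS and BAI are taken at T2 and T3 in both arms, and the HDRS covers suicide and somatic symptoms, so worsening still present at those visits is measured. What lacks a prompt is the discrete or resolved event: an attempt, an admission, an accident. No rule turns a scale score into an adverse event record.

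The missing row in Appendix 2 is weak evidence on its own, since that table also leaves out the MDD-S, SCID-I, WAI and expectancy items described in section 6. The point rests instead on the fact that no other section supplies a question or a time point.

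Finally, the protocol already reports some completed conduct (no adverse events, and the RRS dropped after a printing error), so new collection may come too late. That limits the remedy; it does not remove the problem with the sentence.

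**Conclusion.** The point holds as one of incomplete ascertainment. The protocol defines adverse events over the whole study but provides only unprompted case-file capture, with contact time partly set by BDI-II scores. Under a definition that counts any worsening symptom, in at least 128 planned patients with depression, a report of no events is at least consistent with under-recording and cannot be taken as absence of harm.

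Any bias between arms is possible but not established, and its size and direction cannot be fixed from the document. The ratios in the working depend on assumed weekly sessions, assumed session averages and a constant, equal event rate. The planning means make unequal contact foreseeable only if the planned effect is real and scores are roughly normal. This is a change the sponsor should make, not one on which the primary comparison depends.

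**What to change.** Add to section 8 and Appendix 2 the same short, fixed adverse event enquiry for both arms at T2 and T3. It should cover the time since the last assessment and ask about suicide attempts, admissions, accidents and new or worse symptoms. Ask it after the HDRS has been scored, so that the answers cannot influence the rating. Report events by arm with person-time, separately for the treatment and follow-up periods.

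If those visits have already taken place, reword the sentence in section 8 to say that no adverse events were recorded by unprompted case-file capture.

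The cost is a few minutes at two visits that are already planned, some protocol wording, and a small risk that an answer reveals the treatment to the assessor. Asking last protects the HDRS at that visit, but a disclosure at T2 could carry over to T3. Rewording alone costs nothing but does not recover missed events.

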### **9.1. Sample size**

There are currently no direct comparisons of MCT against CBT for depression to inform sample size estimates. Therefore we plan the current study to detect a post-treatment difference between groups based on mean BDI-II scores observed in previous studies that tested MCT or CBT separately (Dimidjian, Hollon, Dobson et al, 2006; Papageorgiou & Wells, 2015). The mean following MCT was 10 and the mean for CBT 14, suggesting a group difference of 4 points (a standardized effect size of 0.57), we used 7 as the standard deviation (Papageorgiou & Wells, 2015). Using an alpha of 5% and 90% power, this indicated that 64 participants per group were required (total n=128). We plan to increase the target sample by a further 20% to allow for pre-to-post treatment attrition.

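### The adverse-event rule excludes randomised patients from the trial without separating stopping therapy from stopping follow-up or analysis, and conflicts with the case-by-case rule for SAEs

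*Protocol*

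**What the plan says.** Everything at issue stands in section 8 of the protocol (Safety Reporting and Adverse events).

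- **Definition.** An adverse event is any unfavourable, unintended effect during the study that is new since baseline, or that was present at baseline and appears to worsen. Symptoms are named as an example.
- **Capture.** "Information related to an adverse event will be captured in the case file and will be regularly monitored by the research management group".
- **Rule for some events.** "In the case of adverse events like suicide attempts or sudden accidents", the protocol continues, "it was decided to take action and report and exclude patients from the trial in order to get them hospitalised".
- **Result.** The next sentence reads: "However, no adverse events were reported in this trial".
- **SAEs.** The SAE list names suicide attempts (as life-threatening events) and events requiring hospitalisation. For these, "The response to SAE's will be determined on a case by case basis and will be in line with local policies and procedures".

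Appendix 2 schedules the BDI-II at pre-treatment, at sessions, at post-treatment (T2) and at follow-up (T3), and the HDRS at T1, T2 and T3. Section 9.2 says that a statistical analysis plan will be drawn up.

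**The concern.** A suicide attempt in a depression trial is closely tied to the outcome being measured. If it takes a randomised patient out of follow-up or out of the analysis, whether a patient has data depends on how that patient fared. The arm with more such events then looks better than it was. This would touch the two primary outcomes, maintenance over 6 months, recovery rates and the dropout comparison (section 3, aims 1, 3, 4 and 5). Safety follow-up after the event would be lost as well.

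The wording ties hospital care to leaving the trial, although a patient can receive any care and still be assessed. It also gives two rules for the same patient: a suicide attempt leads to exclusion under one sentence and to a case-by-case decision under another.

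Finally, the statement that no adverse events were reported sits under a definition broad enough to include a worsening symptom, in a trial that measures depressive symptoms at every session.

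**Working it through.** **1. The two rules side by side.** The exclusion sentence covers suicide attempts and sudden accidents and fixes the consequence in advance. The SAE paragraph covers suicide attempts and hospitalisation and leaves the response open. A suicide attempt falls under both. Neither sentence says what happens to the T2 and T3 assessments.

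**2. Three meanings of exclusion.**

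| Meaning | Effect on the randomised comparison |
|---|---|
| Trial therapy stops, assessments continue | None from the rule itself |
| Assessments stop | T2/T3 data missing because of outcome |
| Removed from the analysis | Arms no longer compared as randomised |

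**3. The plan's own figures (section 9.1).** Post-treatment BDI-II means are 10 (MCT) and 14 (CBT), SD 7, alpha 5%, power 90%, with 64 per group stated. Two-sided normal formula: n = 2 × (7 × (1.960 + 1.282) / 4)² = 64.4 per arm, 65 when rounded up; power at 64 is 0.898. The stated figure is reproduced within rounding. It serves here only as a base for size.

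**4. Exclusions in one arm.** Assumptions not in the protocol: a fraction f = 2%, 3% or 5% is excluded, and these patients would have scored 35. That score lies in the severe band of 29–63 (section 6.1) and is (35 − 14)/7 = 3 SD above the CBT mean. The mean of those retained is (14 − 35f)/(1 − f), so the arm mean falls by 21f/(1 − f).

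**5. Equal rates in both arms.** The CBT mean falls by 21f/(1 − f) and the MCT mean by 25f/(1 − f). The difference widens by 4f/(1 − f).

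| f | One arm, mean 14 | Share of 4 points | Equal rates | Share of 4 points |
|---|---|---|---|---|
| 2% | 0.43 | 11% | 0.08 | 2% |
| 3% | 0.65 | 16% | 0.12 | 3% |
| 5% | 1.11 | 28% | 0.21 | 5% |

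**6. The same in patients.** With 64 per arm and k excluded at score x, the retained mean is (64 × mean − k × x)/(64 − k). For x from 29 to 50, the planned difference of 4.0 becomes:

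| Excluded | Only from CBT | Only from MCT |
|---|---|---|
| 1 | 3.8 to 3.4 | 4.3 to 4.6 |
| 3 | 3.3 to 2.2 | 4.9 to 6.0 |

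Three from each arm gives 4.2. None gives 4.0. The direction depends on which arm has more events.

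**7. The zero count.** If each of 154 patients (128 × 1.2, the planned total) had an assumed 5% chance of a recordable worsening, the chance of no such event would be 0.95^154 = 0.04%; at 2% it would be 0.98^154 = 4.5%. These rates are assumed, and the protocol does not give the number enrolled. Taking zero at face value, the one-sided 95% upper limit for the event rate is 1 − 0.05^(1/128) = 2.3% with 128 patients, or 1.9% with 154.

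**The case against.** The strongest reply is that the rule appears never to have been used. The sentence after it says that no adverse events were reported, so on the protocol's own account nobody was excluded and the realised shift is zero. Unrecorded mild worsening would not change this, because the trigger is an event such as a suicide attempt or accident, not a rise in BDI-II. This stands. A reader might infer that the trial's results are biased by the rule; the document does not support that.

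A reader might also infer that the worst safety events vanish from the record. The rule says to report as well as exclude, and events go into the case file, so the triggering event is kept. Only follow-up after it is at risk.

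Exclusion may mean no more than stopping therapy, and the analysis set may be defined in a statistical analysis plan that is not shown. This is fair, and it is why the bias is stated conditionally. It does not dispose of the point, because no analysis plan can recover T2 and T3 assessments that were never made.

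The one-arm figures of 11–28% are a worst case on assumed inputs and should not be read as an expected bias. Nor are sudden accidents an outcome of depression in the way that a suicide attempt is.

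Last, it is tempting to call the zero count false. The protocol says that none were reported, not that no symptom worsened, and the small probabilities above rest on assumed rates. The count is doubtful as evidence under so broad a definition; it has not been shown to be wrong.

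**Conclusion.** The point holds as a defect in the written rule. Section 8 excludes patients after randomisation because of an event that can be outcome-related, does not say what exclusion covers, and conflicts with its own case-by-case sentence on SAEs.

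Any bias is conditional on exclusion ending assessments or analysis, and on such events occurring. Under the assumed 2–5% excluded at BDI-II 35, it is about 0.4–1.1 points if all exclusions fall in one arm with mean 14, about 0.1–0.2 points if the rates are equal, and zero if no events occurred. The statement that no adverse events were reported cannot carry a conclusion of no harm in either arm. The protocol does not itself draw that conclusion.

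**What to change.** - Reconcile the exclusion sentence with the case-by-case sentence. The clinical response is for those responsible for care and is not proposed here.
- State that, whatever care is given, every randomised patient stays in T2 and T3 follow-up where they consent, and in the analysis as randomised. Record the event and any discontinuation of therapy.
- Because the text already reports a result, say in the trial report whether any patient was excluded under this rule and, if so, in which arm.
- Do not rely on the zero count to support absence of harm. Report SAEs by arm, with the number of patients whose BDI-II deteriorated, using the sessional scores already collected and a definition of deterioration fixed before the table is made.

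The cost is a few lines of protocol text, follow-up attempts for at most a few patients (none if no one was excluded), and one additional table.
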